## 11 STUDY FLOW SHEET

| Appointment                                                | Time and Range                | Curran Rating
EGFRvIII screen
HIV Screen
Hepatitis | Physical,
Ophthalmologic,
and Neurologic
Exam
MMSE
KPS | MRI  | EGFRvIII PCR
EGFRv III ELISA
Blood for
Autoimmunity and
Immunologic
monitoring  | DTH  | ABC 
T4/T8 | CMP 
β-HCG  |
|------------------------------------------------------------|-------------------------------|-------------------------------------------------------------|-----------------------------------------------------------------------|-------------------|-------------------------------------------------------------------------------------------------------------|-------------------|----------------------------|------------------------------------------|
| Screening and Pre-enrollment                               | Week ≤4 from leukapheresis    | X                                                           |                                                                       |                   |                                                                                                             |                   | X                          |                                          |
| Pre-Immunization Leukapheresis                             | Prior to Temozolomide         |                                                             | X                                                                     | X    | X                                                                                                           | X                 | X                          | X                                        |
| Radiation with Temozolomide                                | 6 ± 2 weeks duration          |                                                             |                                                                       |                   |                                                                                                             |                   | X                          |                                          |
| Initial Temozolomide Cycle                                 | 3 ± 1 week post RT (Days 1-5) |                                                             | X                                                                     | X    |                                                                                                             |                   | X                          |                                          |
| Immunization #1 (Daclizumab)                               | Day 21 ± 2                    |                                                             | X                                                                     |                   | X                                                                                                           |                   | X                          |                                          |
| Immunization #2                                            | Day 35 ± 7                    |                                                             | X                                                                     |                   |                                                                                                             |                   | X                          |                                          |
| Immunization #3(Daclizumab cohort#2)                       | Day 49 ± 7                    |                                                             | X                                                                     |                   |                                                                                                             | X                 | X                          |                                          |
| Temozolomide Cycles                                        | Every 4 weeks (Days 1-5)      |                                                             |                                                                       |                   |                                                                                                             |                   | X                          |                                          |
| Immunization #4 (even) (Daclizumab cohort#2)  | Day 21 ± 2 of cycle           |                                                             | X                                                                     | X                 | X                                                                                                           | X                 | X                          |                                          |
| Immunization #5 (odd)                                      | Day 21 ± 2 of cycle           |                                                             | X                                                                     |                   | X                                                                                                           |                   | X                          |                                          |
| EGFRvIII +DTH                                              | +DTH                          |                                                             | X                                                                     |                   | X                                                                                                           |                   | X                          | X                                        |
| Progression                                                |                               |                                                             | X                                                                     | X                 | X                                                                                                           | X                 | X                          |                                          |

 MRI every 8 ± 4 weeks.

 10 Yellow top ACD (9 mL each) and 3 Red top (9 mL each) - all **prior** to vaccine except prior to vaccines #2 and #3 where only 4 Yellow top ACD (9 mL each) and 3 Red top (9 mL each) will be obtained . With vaccine #4, blood work for immunological monitoring will occur monthly before each vaccine. Blood work for autoimmunity monitoring will be obtained prior to vaccine # 1 and every 4 months after vaccine # 3.

 Should be read 48-72 hours after placement

 All ABC should be obtained with manual differential counts. ABC should always be obtained with T4/T8 counts. These should be obtained at least weekly during concurrent external beam radiation and temozolomide, immediately before and within 1h after ALT, and then subsequently on day of vaccine and immediately prior to next temozolomide cycle.

 Comprehensive Metabolic Panel (CMP)

 Obtained BEFORE each leukapheresis only. B-HCG only required for females.

 MRI here is just post-operative eligibility MRI

 Post-radiation MRI will be done a minimum of 10 days after completing radiation therapy.

 Cohort 2 will receive daclizumab at same dose with vaccine # 1, # 3, and on day 21 ± 2 for 3 TMZ cycles.

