| Exclusion Criteria: | 
 
• Radiographic or cytologic evidence of leptomeningeal or multicentric disease at any time prior to vaccination.
 
• Prior conventional antitumor therapy other than steroids, RT, or TMZ.
 
• Pregnant or need to breast feed during the study period (Negative <math>\beta</math>-HCG test required).
 
• Requirement for continuous corticosteroids above physiologic levels at time of first vaccination.
 
• Active infection requiring treatment or an unexplained febrile (<math>> 101.5^{\circ}</math> F) illness.
 
• Known immunosuppressive disease or human immunodeficiency virus infection.
 
• Patients with unstable or severe intercurrent medical conditions such as severe heart or lung disease.
 
• Allergic or unable to tolerate TMZ for reasons other than lymphopenia.
 
• Patients with previous inguinal lymph node dissection.
 
• Prior treatment with daclizumab for any reason.
 
• Prior allogeneic solid organ transplant.
 
                                                                                                                                                                                                                                                                                                                                                                                                                                                                                                                                                                                                                                                                                                                                                                                                                                                                                                                                                                                                                                                                                                                                                                                                                                                                                                                                                                                                                                                                                                                                                                                                                                                                                                                                                                                                                                                                                                                                                                                                                                                                                                                                                                                                                                                                                                                                                                                                                          |

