#### **4.2.3 Pregnancy**

Females who are pregnant or need to breast feed during the study period will be excluded. A negative  $\beta$ -HCG test will be required within 2 weeks of enrollment.

Patients found to be pregnant will be excluded. Male and female enrolled patients will be advised to practice an effective method of birth control.

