#### **4.2.4      Corticosteroids**

Patients receiving corticosteroids, with the exception of nasal or inhaled steroid, at a dose above physiologic levels will be excluded. Patients requiring an increase in corticosteroids, with the exception of nasal or inhaled steroid, such that at the time of first vaccination they require a dose above physiologic levels, will be removed from the study and replaced. For the purposes of this study, physiologic dose will be defined as <2 mg of dexamethasone / day. Once vaccinations have been initiated, if patients subsequently require increased steroids, they will still be permitted to remain on the study, but every effort will be made to minimize steroid requirements.

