|------------------------------------------------------------------|
| Absolute Neutrophil Count $\geq 1.0 \times 10^9/\text{L}$        |
| Platelet Count $\geq 100 \times 10^9/\text{L}$                   |
| Resolution of CTC Non-hematologic toxicities to Grade 2 or less. |

Because of the risk of opportunistic infections in patients receiving TMZ, patients may receive antibiotic prophylaxis at the discretion of the primary Neuro-Oncologist, consisting of inhaled pentamidine or oral levofloxacin. Antiemetic prophylaxis with metoclopramide or a 5-hydroxytryptamine3 antagonist will also be recommended before the initial doses of concomitant TMZ and may be used during the adjuvant five-day course of TMZ.

During TMZ cycles, dose adjustments to TMZ, if needed, will be conducted as outlined below:

| Table 4: Temozolomide Dose Reduction or Discontinuation During Maintenance Treatment |                                            |                          |
|---------------------------------------------------------------------------------------------|--------------------------------------------|--------------------------|
| Toxicity                                                                             | Reduce TMZ by 25 mg/m^2/d | Discontinue TMZ   |
| Absolute Neutrophil Count                                                                   | $<1.0 \times 10^9/\text{L}$                | See footnote a           |
| Platelet Count                                                                              | $<50 \times 10^9/\text{L}$                 | See footnote a           |
| CTC Non-hematological Toxicity (except for alopecia, nausea, vomiting)                      | CTC Grade 3                                | CTC Grade 4 a |

a: TMZ is to be discontinued if [dose reduction](#) to  $<50 \text{ mg/m}^2$  is required or if the same Grade 3 non-hematological [toxicity](#) (except for alopecia, nausea, vomiting) recurs after [dose](#) reduction.

[figure not shown]

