## **6 DATA AND SPECIMEN COLLECTION**

### **6.1 Pretreatment Evaluation**

#### **6.1.1 Baseline and Eligibility**

To be enrolled, patients must undergo leukapheresis. Clinical and laboratory evaluations will be obtained within 2 weeks of enrollment for the purposes of meeting Inclusion and Exclusion Criteria as outlined in the Study Flow Sheet.

Pathology slides consisting of 1 H&E and 19 unstained slides, from all prior resections or biopsies, prepared on Fischer Plus glass or Histostix coated slides when available will be mailed to:

[name]., Ph.D.  
[name]  
[name]  
Duke University Medical Center  
[name]

Blood samples will also be sent for the following study related tests: T4/T8 ratio (Lab Code 2500202) and, ABC (Lab Code 2010200) with manual differential (Lab Code 2000640).

Initial clinical evaluations will also include a complete physical, ophthalmologic and neurologic examination with KPS rating, MMSE testing, and Curran rating.

A baseline and study eligibility MRI (with and without gadolinium enhancement) of the brain using standard 5 mm slices with 2.5 mm spacing for comparison to subsequent MRI images will also be obtained.

Patients will also be assessed before vaccine # 1 and every 4 months after vaccine # 3 by a panel of clinical laboratory analyses to screen for the development of autoimmunity. The most common manifestations of autoimmunity seen in related trials (Phan, Yang et al. 2003; Attia, Phan et al. 2005; Blansfield, Beck et al. 2005; Jaber, Cowen et al. 2006) have included enterocolitis, dermatitis, uveitis, hepatitis, and hypophysitis. Laboratory evaluations to detect subclinical disease will be obtained as follows: serum thyroglobulin Ab (Lab Code 1802105), rheumatoid factor (Lab Code 5560195), antinuclear Ab (Lab Code 5560214) (Homma, Sagawa et al. 2006); human anti-human (anti idiotypic) Ab ([name] Lab), erythrocyte sedimentation rate (Lab Code 2000860), thyroid-stimulating hormone (Lab Code 1802085), ACTH (Lab Code 1800020), cortisol (Lab Code 1802010), free T4 (Lab Code 1802081), ALT, and AST (Lab Code 1004000). Finally, if cerebrospinal fluid becomes available, it will be checked for oligoclonal banding (Lab Code 1543440).

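### No pregnancy test is scheduled between the pre-temozolomide leukapheresis and vaccine #1 with daclizumab or saline, and the synopsis and section 4.2.4 differ on when the steroid exclusion applies

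*Protocol*

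**What the plan says.** **Pregnancy.** Section 4.2.3 states: "Females who are pregnant or need to breast feed during the study period will be excluded". It sets the test against enrolment ("HCG test will be required within 2 weeks of enrollment"), adds without a date that patients found to be pregnant are excluded, and has patients advised on birth control. Section 6.1.1 uses the same anchor for eligibility in general: "Clinical and laboratory evaluations will be obtained within 2 weeks of enrollment for the purposes of meeting Inclusion and Exclusion Criteria".

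The flow sheet in section 11 marks the CMP and beta-HCG column in two rows only: the pre-immunization leukapheresis, timed "Prior to Temozolomide", and the EGFRvIII +DTH row. The column is blank in every immunization row. Footnote 25 gives the rule: "Obtained BEFORE each leukapheresis only. B-HCG only required for females". Section 5.1.1 places randomisation to daclizumab or saline together with vaccine #1, after radiotherapy and the first adjuvant TMZ cycle.

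**Steroids.** The synopsis lists as an exclusion: "Requirement for continuous corticosteroids above physiologic levels at time of first vaccination". Section 4.2.4 begins with a rule that names no time: "Patients receiving corticosteroids, with the exception of nasal or inhaled steroid, at a dose above physiologic levels will be excluded". It then adds that a patient whose steroids have been increased, so that the dose is above physiologic at first vaccination, is removed and replaced. The physiologic dose is defined there as less than 2 mg of dexamethasone a day.

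**The concern.** The pregnancy exclusion is meant to hold while the investigational agents are given, but testing is tied to a collection procedure that comes months before the first of them. Someone who conceives during radiotherapy or the first adjuvant cycle is excluded by section 4.2.3, yet no scheduled test would reveal it before randomisation. Exposure then continues: vaccines run monthly until progression, and cohort #2 receives serial daclizumab. Any later test depends on a positive PEPvIII skin test, so whether a woman is tested again depends on her immune response and not on her exposure.

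For steroids, two versions of one criterion give different answers for a common type of patient. Section 3.2.3 says that glioblastoma patients are frequently given steroids, which are then tapered, and that steroids are lympholytic. Section 8 takes baseline immune values from the pre-vaccine leukapheresis. Which text a site follows therefore decides who is enrolled and whether some baseline samples are taken on steroids above the physiologic dose.

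**Working it through.** **1. When beta-HCG is scheduled relative to study drug**

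| Step | Beta-HCG in flow sheet |
|---|---|
| Pre-immunization leukapheresis, before TMZ | Yes |
| Radiotherapy with TMZ | No |
| Initial TMZ cycle after radiotherapy | No |
| Immunization #1, with randomised daclizumab or saline | No |
| Immunizations #2, #3, #4 and #5 | No |
| EGFRvIII +DTH (extra leukapheresis) | Yes, if skin test positive |

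The skin-test route does not supply a test before vaccine #1. The sentence on the extra leukapheresis also appears in section 6.2.3, on the period before the first immunization. But section 5.2.3 describes the baseline skin tests as recall antigens, and section 8.7.1 assumes no response before vaccination.

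**2. Length of the untested interval**

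Inputs:
- Radiotherapy: 33 fractions, five per week, in less than seven weeks (section 5.1.2). At five per week, 33 / 5 = 6.6 weeks.
- Break before the first adjuvant cycle: 3 ± 1 weeks (sections 5.1.1 and 11).
- Vaccine #1: day 21 ± 2 of that cycle (sections 5.2.1 and 11).

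Formula: start of radiotherapy to vaccine #1 = radiotherapy + break + day of vaccine / 7.

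- Nominal: 6.6 + 3 + 21/7 = 12.6 weeks.
- Shortest: 6.6 + 2 + 19/7 = 11.3 weeks.
- Longest: 7 + 4 + 23/7 = 14.3 weeks.

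The age of the last test at vaccine #1 is this interval plus any time from leukapheresis to the start of radiotherapy, which the protocol does not fix.

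**3. Check against the protocol's own figure**

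Sections 7.3 and 7.4 put vaccine administration 3 to 4 months after enrolment. At 365.25/12/7 = 4.35 weeks per month, that is 13.0 to 17.4 weeks. The nominal 12.6 weeks from the start of radiotherapy, plus an assumed 1 to 4 weeks from enrolment to radiotherapy, gives 13.6 to 16.6 weeks. The two agree.

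**4. The two steroid texts applied to the same patients**

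| Dose at enrolment | Dose at vaccine #1 | Synopsis | Section 4.2.4 |
|---|---|---|---|
| Physiologic | Physiologic | Eligible | Eligible |
| Physiologic | Above physiologic | Excluded | Removed and replaced |
| Above physiologic | Physiologic (tapered) | Eligible | Excluded at entry |
| Above physiologic | Above physiologic | Excluded | Excluded at entry |

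The third row is a contradiction. In the fourth the patient is out under both texts, but at different times: under the synopsis only after leukapheresis, radiotherapy and one TMZ cycle.

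**The case against.** **Eligibility as a whole.** A reader might infer that eligibility is verified only at enrolment. The protocol does not support that. Steroid dose is checked again at first vaccination (section 4.2.4). TMZ intolerance found after enrolment leads to removal (section 4.2.6). Progression during radiotherapy and PBL release are in the replacement list of section 5.1.1. The synopsis runs the leptomeningeal and multicentric exclusion up to vaccination. This part of the objection stands, and the point is confined to pregnancy testing and the steroid time point.

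**Pregnancy.** A reader might go further and say that a woman who conceives in the interval still meets every written condition for randomisation. She does not: section 4.2.3 excludes anyone found to be pregnant. What is missing is a scheduled test, not the exclusion. Nor is it right that nobody is ever tested again, since a DTH-positive woman has a beta-HCG before her extra leukapheresis. The contraception advice lowers the risk but does not establish status. It is also tempting to set the interval against the two-week window in section 4.2.3, but that window runs to enrolment and sets no standard for first study drug.

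**Infection.** Section 5.1.3 recognises a hazard in the interval ("Because of the risk of opportunistic infections in patients receiving TMZ"), and infection is not in the replacement list. But the infection exclusion in section 4.2.5 carries no date, and a physical examination is scheduled with each vaccine. The text does not show a contradiction, and a further infection rule would be a clinical choice outside this review.

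**Interval.** Using the flow sheet's 6 ± 2 weeks for radiotherapy would give 8.7 to 15.3 weeks. The prescribed course in section 5.1.2 does not allow four or eight weeks, so 11 to 14 weeks is the supportable range.

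**Steroids.** Section 4.2.4 read alone can be taken as two gates in sequence, which is coherent. That is accepted: the conflict is with the synopsis, which has only the second gate. A reader might also infer that steroids at baseline bias the primary result. They do not bias the randomised contrast. The functional assay comparison (section 8.2) and the T-reg count comparison (section 8.3.1) are between randomised groups. Only the pre/post comparisons are exposed, and section 8.3.1 calls its within-group test exploratory.

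**Conclusion.** Two narrow points hold.

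First, the pregnancy exclusion covers the study period, but the schedule contains no test that could detect pregnancy between the pre-TMZ leukapheresis and vaccine #1. The interval is about 11 to 14 weeks from the start of radiotherapy, or 3 to 4 months from enrolment on the protocol's figure. The first range rests on 33 fractions given five per week in under seven weeks. The true age of the last test is longer by any gap between leukapheresis and radiotherapy. After vaccine #1, further testing depends on skin-test response.

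Second, the synopsis and section 4.2.4 classify a patient tapered between enrolment and vaccine #1 in opposite ways. This rests on reading the undated rule in section 4.2.4 as an entry criterion, which the separate first-vaccination rule that follows it supports. The number of such patients cannot be estimated from the protocol. The effect is on who is enrolled and on the baseline used for pre/post comparisons.

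Neither point alters the power statement, the significance level or the between-arm analysis. Both should be corrected because the texts disagree and aligning them is cheap.

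**What to change.** 1. Reconcile section 4.2.3 with footnote 25 and the flow sheet so that pregnancy status is established before first study drug as well as at enrolment. The vaccine #1 visit already includes a pre-vaccination blood draw (section 6.2.4 and the flow sheet), so no new visit is needed. Because randomisation is simultaneous with vaccine #1, the result should be available before allocation, so that an excluded patient is not lost from an arm of 10 after randomisation. The replacement list in section 5.1.1 does not name pregnancy, so the text should also say how such a patient is counted. Cost: one assay for women of child-bearing potential, and having its result in time.

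2. Reconcile the synopsis exclusion list with section 4.2.4 on the time point or points at which the steroid criterion applies, and put a date on the first sentence of section 4.2.4. Which rule is adopted is a clinical decision for the investigators; the need is that both places say the same thing. Cost: one aligned sentence in each place.
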